#### Implementation outcomes and evaluation of implementation pathway

After each of the 12 personal consultations, implementation outcomes (i.e., acceptability, appropriateness, feasibility, and fidelity) will be assessed using quantitative methods via surveys of intervention patients and of the CCs (APNs), who provide the SMILe-ICM (Table 4). The implementation pathway will be evaluated via a qualitative approach after the intervention period with input from the entire alloSCT team and all intervention patients.

**Table 4 Tab4:** Implementation outcomes

Outcome variable(s)	Measure(s) and data collection procedures	Data source and reporter (when applicable)
**Acceptability from patient’s perspective**	Acceptability—reflecting the end users’ satisfaction with the intervention—will be assessed using the 4-item Acceptability of Intervention Measure (AIM). Each item applies a 5-point Likert-type scale ranging from 1 (completely disagree) to 5 (completely agree) with higher scores indicating greater acceptability [90].	Paper survey (pat.)
**Appropriateness from patient’s perspective**	The intervention’s appropriateness, i.e., its perceived suitability to address problems within its target setting, will be assessed via the 4-item Intervention Appropriateness Measure (IAM). Each item applies a 5-point Likert-type scale ranging from 1 (completely disagree) to 5 (completely agree) with higher scores indicating greater appropriateness [90].	Paper survey (pat.)
**Feasibility from patient’s perspective**	The intervention’s perceived suitability for everyday use – will be assessed with the Feasibility of Intervention Measure (FIM). Each item applies a 5-point Likert-type scale ranging from 1 (completely disagree) to 5 (completely agree) with higher scores indicating greater feasibility [90].	Paper survey (pat.)
**Technology acceptability**	The ratio of the number of data entry days to the number of technological problems, will be a measured using data gathered via the SMILeApp.	SMILe monitoring data base (SMILe Care)
**Acceptability from CC’s perspective**	Acceptability—reflecting the end users’ satisfaction with the intervention—will be assessed using the 4-item Acceptability of Intervention Measure (AIM). Each item applies a 5-point Likert-type scale ranging from 1 (completely disagree) to 5 (completely agree) with higher scores indicating greater acceptability [90].	Paper survey (CC)
**Appropriateness from CC’s perspective**	The intervention’s appropriateness, i.e., its perceived suitability to address problems within its target setting, will be assessed via the 4-item Intervention Appropriateness Measure (IAM). Each item applies a 5-point Likert-type scale ranging from 1 (completely disagree) to 5 (completely agree) with higher scores indicating greater appropriateness [90].	Paper survey (CC)
**Feasibility from CC’s perspective**	The intervention’s perceived suitability for everyday use will be assessed with the Feasibility of Intervention Measure (FIM). Each item applies a 5-point Likert-type scale ranging from 1 (completely disagree) to 5 (completely agree) with higher scores indicating greater feasibility [90].	Paper survey (CC)
**Intervention fidelity**	The gold standard measure of intervention delivery (observations/evaluations using prespecified criteria) [95] will be used: Intervention participants’ attendance as planned to face-to-face visits T0 – T8 (fully, partly or not at all) will be noted by the CC. Any deviation from the intervention protocol will be recorded in view of number, length, frequency of contacts, and delivered content.	CRF (RA)
**Implementation pathway**	To explore potential implementation process barriers and facilitators as well as problems experienced in its delivery, we will conduct focus group interviews with the alloSCT team including 10–15 health care professionals (i.e., haematologists, nurses, psycho-oncologists, management), who are involved in the in-patient and follow-up care, plus 10 individual intervention patient interviews.	Individual interviews (pat.)
		Focus group interviews (health care professionals)

*Abbreviations. CC* Care Coordinator, *pat* patient; *RA* Research Assistant

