With the increasing global burden of chronic conditions, more health care systems are recognizing the need to reengineer systems of care based on principles of chronic illness management and powering them with eHealth. This need is reflected in health care policy guidelines on ICMs and eHealth [28, 29], with eHealth also fuelled by the recent COVID pandemic [30, 31]. Further increasing the interest in assessing electronic Patient Reported Outcomes (ePROs) [32], the evidence base from trials testing the effectiveness of eICM shows promising findings [1, 7, 9, 10].

For most eHealth interventions, implementation issues are substantial: 44–67% of patients discontinue the offered eHealth tools. These problems often reflect mismatches between the technologies and their contexts, particularly their target users’ needs [33–35]. The results include low adoption rates (10–12%) [33, 35] and problems with acceptance (64–86.5%) [34]. Further, many eHealth solutions fail either to base their work on acknowledged theories or to build on empirical evidence: only 26% refer to a theory of behaviour change; and only 11.3% are evidence-based [36, 37]. For the moment, then, studies tend to report on mHealth apps’ problems with system interoperability (i.e., lack of integration with electronic health records (EHR)) [35], reimbursement structures [38], security (often resulting from insecure communication protocols), and lack of privacy policies [39]. These issues hinder adoption (e.g., a site may want to use a tool, but it may not be compatible with their EHR package) and sustainability (e.g., a site may have used a tool, but it isn’t compatible after an update) in daily clinical practice. However, even if they were accepted within a given context, their sustainability would likely be rather limited, as their developers rarely address multi-level barriers, i.e., those at the patient, health care provider and health care organizational levels [1, 2]. Therefore, implementation aspects of eHealth solutions in general and of eICMs in particular have largely been disregarded [25, 34]. Afforded little credibility, even the best are often stranded for years in the wasteland between publication and implementation.

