The hospitalisation rate consists of two elements: the number of hospitalisations and the period (in years) over which patients are followed up. We conducted simulations using the paramtest software package [76], computing 10′000 iterations of the chosen parameters. Based on the USB’s available data, we set the hospitalization events per patient year to 1.56. The study’s observation period is 15 months (1.25 years). We determined the minimum sample size using the inverse of the effect size in Schenkel et al. [6], i.e., 1.79 [1.31–2.43]. Following Olivier et al.’s guidance [77], we aimed for the upper bound of a small effect size. The simulation is based on a binomial distribution with a shape parameter of 4. Assuming an α level of 0.05, a power of 80% and an effect size of 1.79, a minimum sample size of 52 patients (26 per group) was determined. Based on a refusal rate of 10% and a 15% drop out rate, then, we will aim to recruit a total of 80 patients (40 per group). Considering that approximately 70 adults per year receive *both alloSCT and follow-up* at USB, recruitment will take a minimum of 16 months.

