**Fig. 4 Fig4:**
[figure not shown]
Consort flowchart

#### Sampling for aim 2

To evaluate the implementation outcomes and pathway (Aim 2), 10–15 health care professionals on the alloSCT care team (i.e., senior and assistant physicians, APNs, professional nurses, nurse leaders and management, psychooncologist, nutritionist) will be invited to participate in the focus group interviews. In addition, 10 individual patient interviews will be conducted between June and December 2022 with all participants’ written consent.

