#### Data collection and management

Data will be collected at pre-defined time points from April 2021 until March 2024 (T0-Tz, see Table 2) by trained APNs using a standardised method in the IG and by one research assistant (using the same method) in the UCG. SMILe data will be de-identified with access limited only to authorized research study team members.

**Table 2 Tab2:** Variables, measurement and data collection points

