***Aim 2:*** Acceptability of Intervention Measure (AIM), Intervention Appropriateness Measure (IAM), and Feasibility of Intervention Measure (FIM) (implementation outcomes) [90] will be descriptively evaluated. Independent Student’s t-tests will be calculated to determine whether implementation outcome scores will change significantly within the IG over the study period. Concerning the analysis of the implementation pathway, field notes, audiotapes of interviews and mind maps of focus group discussions will serve as qualitative data. Transcript data will be stored and analysed in the ATLAS.ti 8 software package [101]. Individual interviews with patients will be thematically analysed following Braun et al.’s six-phase procedure—an approach using stepwise systematic and iterative processing of data to arrive at a meaningful description and interpretation [102]. During the focus group interviews with clinicians, key themes will be mind-mapped on a flipchart to help the researcher recall previous thoughts and summarise all of the focus groups’ input. Participants will have the opportunity to reflect on the maps and to add or change keywords [103]. After the final focus group session, all mind maps will be combined into a single meta-map using the Microsoft Visio Professional 2019 software [104]. We will then apply Mayring’s approach to qualitative content analysis [105].

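### Aim 2 tests change in repeated patient-rated acceptability, appropriateness and feasibility scores with independent t-tests, which ignore pairing and confuse change with loss of respondents; the interview plan also conflicts on numbers and timing

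*Protocol article*

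**What the plan says.** Under Implementation outcomes and evaluation of implementation pathway, the article ties the surveys to visits: "After each of the 12 personal consultations, implementation outcomes (i.e., acceptability, appropriateness, feasibility, and fidelity) will be assessed using quantitative methods". Table 2 schedules the acceptability (AIM), appropriateness (IAM) and feasibility (FIM) measures from T0a to T8, with none at Tz. Data collection and management has the nurses collect the intervention group's data. They also act as care coordinators and hold the consultations.

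The Aim 2 paragraph of Analysis evaluates the three scores descriptively and then applies independent Student's t-tests "to determine whether implementation outcome scores will change significantly within the IG over the study period".

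For the qualitative part, the same implementation-outcomes section states: "The implementation pathway will be evaluated via a qualitative approach after the intervention period with input from the entire alloSCT team and all intervention patients". Sampling for aim 2 says instead that "10 individual patient interviews will be conducted between June and December 2022", and Table 4 also gives 10 patient interviews.

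Other Aim 2 data do not depend on the patient filling in a form. Table 4 records attendance in three grades, including no attendance at all, and deviations in number, length and frequency of contacts. App-entry days come from the monitoring database. Care coordinators complete the three measures as well.

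**The concern.** The scores at T0a and T8 come from the same patients, less those who have stopped. An independent-samples test treats them as two unrelated groups. This has two consequences.

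- It discards the within-patient correlation, so it is insensitive to real change.
- It compares a full early group with a reduced late one. If low raters are more likely to leave, the mean rises although nobody's opinion has changed.

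The nurse who sees the patient is also the data collector, so a patient who stops attending loses contact with the survey too. Low acceptability or feasibility is a plausible reason for stopping, and Aim 2 is meant to inform refinement and scale-up. A rise produced by departures could be read as growing acceptance.

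**Working it through.** The plan gives no figure for these scores or their attrition, so there is none to reproduce. The sample size concerns Aim 1 only.

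**Inputs from the article.** 40 intervention patients and 15% dropout (Sample size determination for aim 1); a 1–5 item scale (Table 4); and, as an upper scenario only, the Background statement that "44–67% of patients discontinue the offered eHealth tools".

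**Assumptions, not in the article.** Score SD 0.8; within-patient correlation ρ = 0.6; leavers lower by D = 0 to 1.5 points; no true change in anyone; an early visit compared with a late one.

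**1. Cost of ignoring the pairing.** For n patients measured twice, the variance of the mean change is 2σ²(1−ρ)/n. The independent test uses 2σ²/n, so its standard error is too large by 1/√(1−ρ). This factor is 1.20 at ρ = 0.3, 1.58 at ρ = 0.6 and 2.24 at ρ = 0.8. At ρ = 0.6 the effective critical value is 1.96 × 1.58 = 3.10 instead of 1.96.

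**2. Shift from departures.** Let stayers average μ and leavers μ − D, with share d leaving. The early mean is μ − dD and the late mean is μ, so the apparent rise is d × D. At 15%, 6 of 40 leave: 0.15 × 0.5 = 0.075, 0.15 × 1.0 = 0.15 and 0.15 × 1.5 = 0.225.

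**3. False significant rises.** Each cell gives the apparent rise in points, then the percentage of 20,000 simulated trials in which the independent test shows a significant increase. A correct two-sided 5% test would do so in 2.5%.

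| Share lost (n left) | D = 0 | D = 0.5 | D = 1.0 | D = 1.5 |
|---|---|---|---|---|
| 15% (34) | 0; 0.2% | 0.08; 1.1% | 0.15; 2.9% | 0.23; 6.6% |
| 44% (22) | 0; 0.5% | 0.22; 9.1% | 0.45; 43.3% | 0.68; 82.9% |
| 67% (13) | 0; 0.9% | 0.34; 18.7% | 0.68; 68.6% | 1.01; 96.5% |

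A paired test in those still measured rejected in 4.9% to 5.4% of runs (two-sided) throughout.

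**4. Interview window.** Data are collected "from April 2021 until March 2024", the intervention runs to one year post-transplant, and "recruitment will take a minimum of 16 months". To finish by December 2022 a patient must be transplanted by about December 2021. April to December 2021 is 9 months, and 9/16 = 56% of the shortest recruitment period. If recruitment used all the time that the data-collection end allows (March 2024 minus 455 days, about the end of December 2022, so 21 months), the share is 9/21 = 43%. Both figures assume even recruitment.

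**The case against.** A reader might infer that patients who stop disappear from Aim 2, that scores must rise through attrition, and that the interviews reach only completers. The documents support none of these.

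- Attendance, app-entry days and care-coordinator ratings remain available for patients who stop. They record that a patient stopped, or how staff rate SMILe. They do not give the patient's own rating.
- A rise requires leavers to score lower. The article describes substantial first-year mortality, and loss through death or relapse need not follow acceptability. With no deficit the shift is zero.
- The 44–67% figure is a general statement about eHealth tools. It is not a rate of leaving nurse consultations, which are planned alongside routine outpatient visits. A patient who abandons the app can still attend and score it low. The plan's own figure is 15%, where the shift is small.
- No section restricts interviews to completers. A patient who stopped early could still be interviewed later, and 40 × 9/16, about 22 patients, is ample for 10 interviews.

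It is also fair that exit procedures may stand in the full protocol that the article condenses, that multiple imputation is under consideration, and that these scores are mainly descriptive and come second to effectiveness. Imputation would not turn an independent test into a paired one. The test is stated in the article, as is the conflict over the interviews, so both can be judged from it.

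**Conclusion.** The point holds in a limited form. The independent t-test is the wrong method for change within one group. At the planned 15% dropout its surest defect is insensitivity: with no leaver deficit it rejects in 0.4% of runs (two-sided) instead of 5%. Departures add an apparent rise of about 0.08 to 0.23 points if leavers score 0.5 to 1.5 points lower, and serious false positives appear only with much heavier loss. The rejection rates rest on the assumed SD, correlation and leaver deficits; the d × D shift rests only on the deficit and the share lost.

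The problem is confined to patient-rated AIM, IAM and FIM and does not touch Aim 1. Separately, the article gives two incompatible accounts of the interviews: 10 patients or all intervention patients, and a fixed calendar window or after the intervention. Both timings can be met only for patients transplanted by about December 2021.

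**What to change.** 1. In Analysis, Aim 2, replace the independent t-tests with a within-patient analysis: a paired test between named visits, or a mixed model over T0a to T8. Aim 1 already uses mixed models for repeated data. This costs nothing beyond the wording. A paired test describes change among those who stayed, so it needs item 2 beside it.
2. Report the number responding at each visit, and show scores by discontinuation status.
3. Add one optional 12-item AIM/IAM/FIM form, with date and reason, when a patient stops, for those who agree. The burden is one short form per patient who stops. Some will decline, and a form completed away from a visit differs in mode, so it should be shown separately.
4. Reconcile the implementation-outcomes section with Sampling for aim 2 and Table 4 on the number of patients interviewed, and state whether the June to December 2022 window or the end of each patient's intervention governs the timing. This is an edit only.

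Reserving interview places for patients who stopped would be reasonable, but it is a matter of preference and not needed to correct the plan.

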#### Analysis

Statistical analyses will be conducted at the University of Basel’s Institute of Nursing Science using the R software package [96]. Data cleaning will include systematic screening for out-of-range values and data inconsistencies. Multiple imputations will be considered for missing data. Descriptive statistics will be applied as appropriate for all variables.
***Aim 1a:*** To determine whether hospitalisation rates (primary outcome) are reduced via the SMILe-ICM’s implementation, we will analyse any differences between IG and UCG rates by applying generalised linear mixed models (GLMM) [97]. The relevant variables (i.e., time, study group, and group x time interaction) will be entered into the models. Our targeted test statistic is the rate ratio by unconditional maximum likelihood estimation (Wald) as described by Rothman et al. [98] and implemented in epitools [99]. We will conduct intention-to-treat and per-protocol analysis. Two-sided significance will be set at 0.05. To analyze the target secondary outcomes over the course of time, descriptive analyses will be carried out and GLMM will be used to determine differences between the IG and UCG. Cost data will be collected and analysed quarterly. Overall survival will be analysed using the Kaplan-Meier method and the log-rank test. To analyse QALY, we will use the EQ-5D-5L**©** value set for Germany. The electronically compiled dosing history will be analysed using by applying GLMM, which account for dependence among observations from a single patient over time. The resulting estimates will be expressed as odds ratios (ORs) [100].
***Aim 1b:*** To test a potential wane-out effect of the SMILe-ICM’s intervention effect over 3 months’ post-intervention follow-up, differences between the IG and the UCG will be determined by applying GLMM. This approach allows calculation of the main group and time effects, and of group-by-time interaction effects. Two-sided significance will be set at 0.05.
***Aim 2:*** Acceptability of Intervention Measure (AIM), Intervention Appropriateness Measure (IAM), and Feasibility of Intervention Measure (FIM) (implementation outcomes) [90] will be descriptively evaluated. Independent Student’s t-tests will be calculated to determine whether implementation outcome scores will change significantly within the IG over the study period. Concerning the analysis of the implementation pathway, field notes, audiotapes of interviews and mind maps of focus group discussions will serve as qualitative data. Transcript data will be stored and analysed in the ATLAS.ti 8 software package [101]. Individual interviews with patients will be thematically analysed following Braun et al.’s six-phase procedure—an approach using stepwise systematic and iterative processing of data to arrive at a meaningful description and interpretation [102]. During the focus group interviews with clinicians, key themes will be mind-mapped on a flipchart to help the researcher recall previous thoughts and summarise all of the focus groups’ input. Participants will have the opportunity to reflect on the maps and to add or change keywords [103]. After the final focus group session, all mind maps will be combined into a single meta-map using the Microsoft Visio Professional 2019 software [104]. We will then apply Mayring’s approach to qualitative content analysis [105].

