#### Randomization process

Intervention patients will receive standard care plus the SMILe-ICM. The usual care group (UCG) will receive standard care. Patients will be randomly allocated 1:1 to the intervention group (IG) or UCG at hospitalisation, i.e., approximately 10 days pre-transplant. Randomization will be stratified by risk group according to age (>/< 65 years), gender (male/female) and living alone (yes/no). The concealed randomization procedure will be implemented via the secuTrial® web-based clinical data management system provided by the USB’s Clinical Trial Unit. After randomization and allocation, no further blinding will be feasible in any group. The study’s duration will be from approximately 10 days pre-transplant to one-year post-transplant, with 3 months’ follow-up after cessation of the intervention period to test for a wane-out effect. A CONSORT flowchart for patients is presented in Fig. 4.

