**Secondary outcomes**												
Healthcare utilisation costs	FIMA**©** (10 Items) [83]			**X**	**X**	**X**	**X**	**X**	**X**	**X**	**X**	**X**
	Swiss standardised unit costs [84, 85]			**X**	**X**	**X**	**X**	**X**	**X**	**X**	**X**	**X**
Length re-hospitalizations	FIMA**©** (10 Items) [83] Medical Records, CRF			**X**	**X**	**X**	**X**	**X**	**X**	**X**	**X**	**X**
Medication adherence (implementation & persistence dimension [67])	Electronic Monitoring: MEMS® Button [86]											
	BAASIS**©** (implementation 4 items; persistence: 1 item) [87]		**X**	**X**	**X**	**X**	**X**	**X**	**X**	**X**	**X**	**X**
Treatment burden	PETS**©** (60 items) [88]	**X**			**X**			**X**			**X**	
Health-related Quality of Life	EQ-5D-5L**©** (5 items) [89]	**X**	**X**	**X**	**X**	**X**	**X**	**X**	**X**	**X**	**X**	**X**
Quality-Adjusted Life Year (QALY)	EQ-5D-5L**©** (5 items) [89], value set for Germany EQ-VT v. 2.0 (116)	**X**	**X**	**X**	**X**	**X**	**X**	**X**	**X**	**X**	**X**	**X**
Incidence/grade chronic and acute GvHD	Medical record, CRF		**X**	**X**	**X**	**X**	**X**	**X**	**X**	**X**	**X**	
Overall survival rate	Medical record, CRF		**X**	**X**	**X**	**X**	**X**	**X**	**X**	**X**	**X**	**X**
Conditioning regimen	Medical record, CRF	**X**										
Donor match/type	Medical record, CRF	**X**										
Disease	Medical record, CRF	**X**										
Disease status at transplant	Medical record, CRF	**X**										
If death: Date and cause of death	Medical record, CRF		**X**	**X**	**X**	**X**	**X**	**X**	**X**	**X**	**X**	**X**
If relapse: Date of relapse	Medical record, CRF		**X**	**X**	**X**	**X**	**X**	**X**	**X**	**X**	**X**	**X**

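### The primary-outcome model omits the three factors by which randomisation is stratified, which makes a dispersion-aware test conservative and can cost power

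*Protocol article*

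**What the plan says.** **Design.** In Randomization process: "Patients will be randomly allocated 1:1" and "Randomization will be stratified by risk group according to age (>/< 65 years), gender (male/female) and living alone (yes/no". The three binary factors define 2 × 2 × 2 = 8 strata. Table 2 (Demographics) shows age, sex and living alone recorded at T0a, ten days before transplant.

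**Primary analysis.** In Analysis, Aim 1a, the arms are compared "by applying generalised linear mixed models (GLMM". The terms are then named: "The relevant variables (i.e., time, study group, and group x time interaction) will be entered into the models". The next sentence adds: "Our targeted test statistic is the rate ratio by unconditional maximum likelihood estimation (Wald", citing a contributed R package. No covariate is attached to that ratio. Testing is two-sided: "Two-sided significance will be set at 0.05".

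**Elsewhere.** No section of the article enters a stratification factor into any analysis. For secondary outcomes it says only that GLMMs will be used, without a term list.

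**The concern.** Stratified allocation holds the arms close to balance on the three factors, so differences between strata contribute little to the real sampling error of the treatment contrast. A model without the factors still counts those differences as unexplained between-patient variation. Its standard error is then larger than the design warrants, and the test rejects less often than its nominal level.

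The list of terms is introduced by an i.e., so it reads as complete for the primary model. This is a stated specification and not a detail left open for a later analysis plan. At stake is power in a trial of 80 patients.

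**Working it through.** **Inputs from the article (Sample size determination, Randomization process, Table 3).** Control rate 1.56 per patient-year; rate ratio 1.79; two-sided 0.05; shape parameter 4, read here as negative binomial size 4; minimum 26 per group; 80 recruited; 15% drop-out, so 80 × 0.85 = 68; primary outcome window one year.

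**Assumed, because the article gives no figures.** Factor prevalences 25%, 40% and 20%; the same rate ratio g for each factor.

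**Step 1: the plan's own figure.** "Assuming an α level of 0.05, a power of 80% and an effect size of 1.79", the article obtains 52 patients. Take the crude statistic z = ln(rate ratio)/√(1/a + 1/b), where a and b are the event totals, with size-4 counts. Simulated power for 1.56 against 1.56 × 1.79 = 2.79 over one year is 79.2% at 25 per group and 80.4% at 26, so 26 per group is reproduced. It is not reproduced at the stated 1.25 years: 86.4% for 1.56 against 2.79, and 68.2% for 1.56 against 0.87. No stratification factor enters this calculation.

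**Step 2: the mechanism by hand, 40 per arm, one year, 1.56 against 1.56/1.79 = 0.872.** Let K be the product over the factors of (1 − p + pg²)/(1 − p + pg)².
- A model without the factors sees variance per arm of [1/μ + 1.25K − 1]/40.
- Under balanced stratified allocation the real sampling variance is [1/μ + 0.25K]/40.
- At g = 2: K = 1.120 × 1.122 × 1.111 = 1.397. The extra-Poisson terms are 1.25 × 1.397 − 1 = 0.746 and 0.25 × 1.397 = 0.349.
- SE without the factors: √[(0.641 + 0.746 + 1.147 + 0.746)/40] = 0.286.
- Real SE: √[(0.641 + 0.349 + 1.147 + 0.349)/40] = 0.249.
- With ln 1.79 = 0.582, power without the factors is Φ[(0.582 − 1.96 × 0.286)/0.249] = 53%. With a correct SE it is Φ[0.582/0.249 − 1.96] = 65%.
- Null rejection without the factors is 2Φ(−1.96 × 0.286/0.249) = 2.4%.

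The same formula gives 64% against 67% at g = 1.5 (K = 1.116), 66% against 68% at g = 1.3 (K = 1.045), and 68% for both at g = 1.

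**Step 3: simulation.** Power without / with the three factors as main effects, one-year window:

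| g | N = 80, negative binomial model (2,000 runs) | N = 68, dispersion-corrected test, t reference |
|---|---|---|
| 1.0 | 70.5% / 71.0% | 59% / 59% |
| 1.3 | 67.8% / 68.5% | 59% / 60% |
| 1.5 | 64.4% / 68.2% | 55% / 59% |
| 2.0 | 56.8% / 67.0% | 43% / 57% |

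Monte Carlo error in the N = 80 column is about 1 point. A further N = 68 run with 1,500 trials gave gains of 2.4, 4.1 and 14.0 points at g = 1.3, 1.5 and 2.0.

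**Step 4: type I error.** At N = 80, for g = 1.0, 1.3, 1.5 and 2.0, null rejection is 5.5%, 4.8%, 5.2% and 3.7% without the factors, and 6.2%, 5.8%, 6.4% and 6.8% with them. At N = 68 with a t reference it falls to 3.1% without the factors, against 4.9–6.1% with them.

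**The case against.** **The gain is mostly recalibration.** This stands. Step 2 uses the same real sampling error on both sides, because stratified allocation has already delivered the precision. In a 68-patient, 15-month run with factor ratios 1.8/1.8/1.4, nominal power was 59.1% against 67.9%, but null rejection was 3.7% against 6.5%. With both tests set to 5% size, power was 63.2% against 62.8%. What is lost is power through an over-wide standard error. Part of any apparent gain comes from a slightly liberal adjusted test, which is why a small-sample reference belongs in the fix.

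**Weak factors.** This also stands. The article gives no prognostic strengths, and up to a ratio of 1.3 the loss is negligible.

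**Stronger readings that a reader might infer, and why the article does not support them:**
- *The stated test statistic has too large a standard error.* Read as a crude Poisson ratio, its standard error comes from event counts and has no residual term. It rejected in roughly 9–14% of null simulations under the plan's own dispersion, so its standard error is too small. That is a separate fault. The conservatism described here belongs to the GLMM or another dispersion-aware test.
- *Baseline quality of life and treatment burden are discarded.* The term list follows the primary-outcome sentence. For secondary outcomes the article names only GLMMs, and nothing says how T0a is handled. It may enter as the first time level, in which case group by time already uses it. A variance saving equal to the squared baseline correlation presumes an analysis that the article does not describe.
- *The log-rank test should have been stratified.* The article does not go into that detail, and a condensed article may leave it to the analysis plan.

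**Conclusion.** The point holds for the primary outcome. The design stratifies on three factors, the stated model terms exclude them, and the stated rate ratio has no place for them. The consequence is a conservative test in any model that estimates between-patient variation. The loss is about 0 to 1 point of power for factor rate ratios up to 1.3 (2 points in the smaller run), about 4 points at 1.5, and about 10 to 14 points at 2.0. These figures rest on the assumed prevalences and prognostic strengths, on size-4 counts and on a one-year window. The omission neither biases the rate ratio nor inflates type I error. It is worth correcting because adjustment costs almost nothing if the factors are inert, and because simulated power in this setting is already below the planned 80%.

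**What to change.** In Aim 1a, add age group, gender and living alone, as used for randomisation, to the primary model as three main effects. Do not fit eight cells: under the assumed prevalences the rarest cell holds 0.25 × 0.40 × 0.20 = 2% of patients, or 1.6 of 80. Take the rate ratio and its test from that model with dispersion estimated and a small-sample reference such as t, and keep the crude Wald ratio as a sensitivity analysis. The cost is one sentence and three degrees of freedom; all three variables are already recorded at T0a.

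As a secondary suggestion only, adjust the QALY comparison for T0a EQ-5D-5L utility. Table 3 builds QALYs from utilities over time, so a chance baseline difference can carry through. That value is already collected. Because T0a and randomisation both fall about ten days before transplant, confirm that it is measured before allocation is known.
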